### Non-coding RNA

Pre-treatment biopsies will be collected from all patients. Total RNA will be extracted, and the quality evaluated. A two-stage approach will be adopted to identify micro-RNAs that are associated with response of rectal tumours to CRT. In the discovery stage Next-Generation Sequencing (NGS) will be used to compare micro-RNA expression within 20 patients in each arm. In the validation stage, we will employ RT-PCR assays to determine the relative micro-RNA levels in a larger set of tissue specimens with known clinical outcomes (N = 35 in each arm). Correlations will be established between the levels of a defined micro-RNA panel and therapeutic response.

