#### Central review and specimen collection

Central tissue collection: paraffin-embedded tissue blocks will be collected for central histology review and for translational studies. Fresh tissue will be collected for biomarker studies.

Central blood collection: blood collection is required for all study patients. Serum and plasma for biomarkers will be collected and initially processed at each site. The frozen samples will be sent to a central lab for analysis.

Central imaging collection: Central Review: MRI scans will be reviewed centrally.

Other central collection: stool specimens will be collected and will be studied centrally to assess for gut microbiome. If there are available samples which have been collected and stored and they meet the sample requirements per the lab manual, these may be used in addition to or in place of collecting new samples.

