### Statistical considerations

#### Sample size

The sample size is determined by utilizing the precision of the expected rate of local failure for patients with cCR after CRT. Based on available literature, the failure rate by 3-years is assumed to be 5%. A sample of 50 participants with cCR will be required to allow for 47 assessable participants (considering 5% potential drop out). This sample size calculation provides a precision of ± 10% with 95% confidence for the estimate of 5% local failure rate. Expecting 20% rate of cCR, this will translate into a total of 250 participants to be enrolled into the study to result in 50 participants in the watch and wait arm. (50 participants in the watch and wait arm and 200 in the standard management arm).

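### Micro-RNA discovery (20) plus validation (35) needs 55 watch and wait patients, but 50 are planned, so at the planned size at least 5 validation patients must also be discovery patients

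*Protocol article*

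**What the plan says.** The Non-coding RNA section describes a two-stage study of micro-RNAs associated with tumour response to chemoradiotherapy. The material is the participants' own: "Pre-treatment biopsies will be collected from all patients". Discovery uses next-generation sequencing to "compare micro-RNA expression within 20 patients in each arm". Validation then uses RT-PCR in "a larger set of tissue specimens with known clinical outcomes (N = 35 in each arm"). The section does not say whether the 35 are different people from the 20, and it names no cohort outside the trial.

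The Sample size section gives the arm sizes: "Expecting 20% rate of cCR, this will translate into a total of 250 participants to be enrolled", that is, "50 participants in the watch and wait arm and 200 in the standard management arm". The 50 is therefore an expected number, since arm membership depends on who reaches clinical complete response (cCR).

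**The concern.** A validation stage is meant to test the panel on patients who had no part in choosing it. Discovery picks the few micro-RNAs that happen to differ most between two groups of 20, and part of that difference is chance. A patient who appears again in validation brings the same chance difference along, so the panel looks predictive even when it is not.

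The two sizes fixed in the protocol cannot both be met by separate patients in a watch and wait arm of 50. Some reuse is built in, and its extent is left open. At stake is the credibility of any claim that a micro-RNA panel predicts response. Predicting cCR from non-coding RNA is one of the listed secondary objectives, and the Background gives discovery and validation of cCR biomarkers as an aim.

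**Working it through.** **Inputs.** Discovery 20 per arm and validation 35 per arm (Non-coding RNA). Total enrolment 250, expected cCR rate 20%, arms of 50 and 200 (Sample size).

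**The plan's own arm sizes.** 250 × 0.20 = 50 and 250 × 0.80 = 200. Both reproduce.

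**Minimum overlap.** Overlap ≥ max(0, 20 + 35 − arm size).
- Watch and wait: 55 − 50 = 5, which is 5/35 = 14% of its validation set.
- Standard management: 55 − 200 is negative, so no overlap is forced.
- If the set of 35 is meant to contain the first 20, the overlap is 20/35 = 57%.
- The largest separate watch and wait validation set is 50 − 20 = 30.

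**What would remove the shortfall.** 55 watch and wait patients need 55/0.20 = 275 enrolled, or a cCR rate of 55/250 = 22%. With 250 enrolled, the exact binomial chance of 55 or more is 24% at a true rate of 20%, 52% at 22% and 88% at 25%. These figures allow for no loss to biopsy or RNA quality.

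**Effect on validation.** The protocol gives neither the number of candidate micro-RNAs nor the selection rule, so these are assumptions: no true signal, 800 independent normal candidates, the best 5 by AUC in 20 versus 20 combined as a signed sum, and identical values on both platforms. The panel is then scored in 35 versus 35. A false validation is an AUC more than 1.96 null standard errors above 0.5 (one direction, nominal 2.5%). With 3,000 runs per row:

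| Patients reused | Mean AUC | False validation rate |
|---|---|---|
| None | 0.50 | 2% |
| 5, watch and wait only (the forced minimum) | 0.54 | 7% |
| 20, watch and wait only | 0.65 | 63% |

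Other runs of the same set-up gave about 6% to 8% for the forced overlap and about 61% for 20 reused in the watch and wait arm. With 400 or 2,000 candidates the forced overlap gives 6% and 8%, and reuse of 20 gives 56% and 69%.

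**Precision lost by keeping the sets apart.** The null standard error of an AUC with group sizes m and n is √[(m + n + 1)/(12mn)].
- 35 versus 35: √(71/14,700) = 0.0695.
- 30 versus 35: √(66/12,600) = 0.0724, about 4% larger.
- 30 versus 42: √(73/15,120) = 0.0695, so 7 more standard-arm specimens recover the loss. After discovery that arm has 180 left.

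**The case against.** - **The text never says the sets are separate.** A larger set can be one that contains the first 20, measured again on a second platform; then 35 fits within 50 and nothing is miscounted. This stands as a reading, and the fault is not a contradiction between two stated totals. But it makes the statistical problem worse, because 20 of the 35 watch and wait patients would be reused in a step called validation.
- **The specimens may come from outside the trial.** The protocol allows suitable stored samples: "these may be used in addition to or in place of collecting new samples". That sentence in the central collection section identifies no separate cohort, and sizing both stages by arm points to the trial's own arms. If outside specimens are meant, the text should say so.
- **Fifty is only an expectation.** True. Total neoadjuvant therapy is allowed, and the Background quotes about 30% pathological complete response with it against 15% with chemoradiotherapy, so more than 20% cCR is plausible. The shortfall holds at the planned number and is not a certainty. On the plan's own 20%, though, the chance of reaching 55 is only 24%.
- **An article leaves specimen allocation to other documents.** This covers which patients go where. It does not cover two fixed sizes that separate patients cannot fill at the planned arm size.

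Two stronger readings are tempting. A reader might start from the sentence "A sample of 50 participants with cCR will be required to allow for 47 assessable participants (considering 5% potential drop out") and infer a forced overlap of 55 − 47 = 8. But that drop-out allowance belongs to the sample size calculation for local failure. The micro-RNA question concerns response, measured on pre-treatment biopsies and known at allocation, so a patient lost later can still contribute. A reader might also conclude that the validation is worthless: reuse of all 20 in both arms gives an AUC of about 0.78 and a false validation rate near 100%. Nothing in the numbers forces that. The standard arm needs no reuse, and up to 30 of the 35 watch and wait patients can be independent.

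**Conclusion.** The point holds at the planned numbers and only for the watch and wait arm. At least 5 of its 35 validation patients must have helped select the panel, and the text leaves open anything up to 20. The forced minimum is a modest but real bias, roughly two to three times the nominal 2.5% error; full reuse in that arm would make a false validation more likely than not.

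The overlap counts rest only on the protocol's figures and on the validation specimens coming from trial patients. The error rates also rest on the assumed candidate number, panel rule and identical assay values. Noise between the two platforms would lower them, so they are an upper guide for these settings.

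The matter deserves correction before specimens are assigned. It concerns one assay within a secondary objective and touches no co-primary endpoint, stopping rule or allocation decision.

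**What to change.** State in the Non-coding RNA section that no patient used in discovery enters the validation set. Set the watch and wait validation size to the patients who remain: about 30 of the planned 50, rising to 35 if enough reach cCR. Keep 35 or more in the standard arm. If specimens from outside the trial are intended, name that set instead and say how its patients correspond to the two arms.

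The cost is a sentence or two of wording and a slightly wider interval from about 30 rather than 35 watch and wait specimens. The roughly 4% loss can be recovered by running about 7 more standard-arm assays. No visit, treatment or enrolment target changes.

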### ctDNA

The study will assess the impact of ctDNA in predicting recurrence in patients in the watch and wait arm: original tumour biopsy tissue will be analyzed with whole exome sequencing for somatic variants. The identified variants will be queried and quantified in plasma using the SaferSeqS assay.[41] We plan to explore baseline ctDNA levels as prognostic markers and change in levels over time as lead indicators of cancer recurrence.

### Methylated DNA

Blood will be collected prior to neoadjuvant treatment and at defined time-points from patients in the watch and wait arm. Methylated *BCAT1* and *IKZF1* will be studied as previously described.[42–44] The prognostic influence of ctDNA methylation will be determined through correlation of methylation and clinical outcomes (response, recurrence and survival). Marker evaluation pre and post CRT will also be assessed and correlated with cancer recurrence in the watch and wait arm. Emergence of methylated DNA after previous clearance will also be correlated with clinical cancer recurrence, and this marker may provide an early indication of cancer persistence or regrowth, ahead of imaging changes.

### TILs

The role of TILs in predicting response to treatment will be assessed. Pre-treatment specimens will be collected. TILs will be measured based on the methodology proposed by the International Immunooncology Biomarkers Working Group. [32, 33] The correlation between TILs and response to neoadjuvant treatment will be assessed.

### Microbiome

The gut microbiome will be evaluated as a predictor of response to CRT. Stool specimens will be collected from participants before starting CRT and after finishing CRT. We will use 16S rRNA gene amplicon sequencing to assess the microbiome as previously described.[45] We will then investigate the correlation between microbiome characteristics (including composition and diversity) and clinical outcomes (including response to neoadjuvant therapy).

### Organoids

A biopsy will be collected from pre-treatment colonoscopy. Organoids will be grown from the biopsy as previously described.[46] These organoids will be expanded for 2 weeks and then subjected to 5-FU as the common agent used in CRT. This will be followed by gamma-irradiation to complete the CRT protocol, mimicking standard neoadjuvant CRT for rectal cancer. Cell viability will be measured generating an ‘area under the curve’ (AUC) value for each organoid in response to CRT. We will then determine whether organoid culture can be used as a biomarker to predict sensitivity to neoadjuvant treatment for rectal cancer patients. We will also use the established cultures for future basic and translational research.

### PROMs

#### Quality of life

Quality of life will be measured using the EORTC QLQ-C30 (ver-3.0) and EORTC QLQ-CR-29 (ver-2.1) questionnaires. EORTC QLQ-C30 (ver-3.0) is a validated questionnaire developed to assess the quality of life of cancer patients.[47] QLQ-CR-29 is a validated questionnaire developed to assess the quality of life of patients with a history of colorectal cancer and is used in addition to the EORTC QLQ-C30 questionnaire.[48].

#### Health related quality of life

Health-related quality of life is a multi-dimensional concept that includes domains related to physical, mental, emotional and social functioning. This outcome will be measured using a validated questionnaire: the EQ-5D-5L questionnaire. This is a widely used generic preference-based tool to measure the health-related quality of life and is commonly used to elicit health utility scores for health economic evaluation.[49].

#### Bowel related quality of life

This outcome encompasses multiple aspects of bowel function and will be measured using the Memorial Sloan Kettering cancer center bowel function instrument (MSKCC BFI)[50] and low anterior resection syndrome score (LARS score)[51].

#### Fear of cancer recurrence (FCR)

FCR is defined as feeling anxious about cancer coming back and is measured by a shorter form of the fear of cancer recurrence inventory- short form (FCRI-SF). FCRI-SF is a tool used for e screening of clinical levels of FCR.[52] To interpret the FCR results, and to measure response efficacy we will use a modified response efficacy scale specifically designed for this study. (Response efficacy scale: supplementary file-3).

#### Survivorship and supportive care needs

Ongoing supportive care needs across the survivorship continuum will be measured using cancer survivors' unmet needs measure (CaSUN). This is a tool, developed to evaluate a self-reported measure of cancer survivors’ supportive care needs.[53].

#### Cost effectiveness

To determine the cost effectiveness of the watch and wait approach, a within-trial economic evaluation from a healthcare sector perspective will be conducted using a cost-utility analysis (CUA), in which the effectiveness will be measured by quality-adjusted life-years (QALYs). The cost-utility analysis involves estimating the incremental cost effectiveness ratios (ICERs) of the watch and wait approach versus standard management plan. For the within-trial economic evaluation, only costs and effects that accumulate within the trial participation up to 24 months will be considered.

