## Background

Rectal Cancer is a common malignancy [1], comprising one third of all colorectal cancer cases [2]. In patients with non-metastatic locally advanced rectal cancer (stage II or III), the current standard management approach involves pre-operative (neoadjuvant) chemotherapy and radiotherapy followed by total mesorectal excision. Neoadjuvant chemoradiotherapy (CRT) is also recommended in patients with extramural vascular invasion (EMVI)—detected by magnetic resonance imaging (MRI)—as EMVI has been identified as a risk factor that predicts relapse, regardless of T and N stage.[3] Surgical resection of the rectum involves a mortality risk and can lead to considerable morbidity, including serious complications such as anastomotic leak.[4, 5] Other possible complications following rectal cancer resection include sexual and urinary dysfunction, which can occur in up to 25% of patients treated by radical surgery, even with meticulous nerve-sparing procedures and in highly specialized centres.[6].

Preoperative CRT can reduce the size of the primary tumour and the depth of tumour penetration and can potentially sterilize the involved lymph nodes. Large randomized studies have established preoperative CRT as the preferred treatment option for patients with stage II or III rectal cancer.[7–11] More recently, studies have shown that the addition of combination chemotherapy to either a short course of radiotherapy or standard long course concurrent CRT before surgery, can improve outcomes.[12–14] This approach is called total neoadjuvant therapy (TNT).

In some patients, preoperative CRT can lead to pathological complete response. Pathological complete response is established when no viable malignant cells are found in the resected surgical specimen. Patients who achieve pathological complete response have better outcomes.[15] Pooled analysis of data shows the rate of pathological complete response to be approximately 15% with CRT and 30% with TNT.[16] Establishing pathological complete response requires examination of the surgical specimen. In patients who have not had surgery, clinical complete response (cCR) is used as a surrogate for pathological complete response. cCR is established when no malignancy is found on clinical examination, imaging, endoscopy (sigmoidoscopy) and biopsy.[15, 17] Surgery may not be necessary in these patients. This approach is known as watch and wait.

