### Design

This is a Longitudinal Cohort Study.

Eligible subjects, after consent/registration, will complete CRT and then based on response will be allocated to one of the two study arms.

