#### Registration

Subjects must meet all the inclusion criteria and none of the exclusion criteria to be eligible for this study. Subjects must be registered before entering the study. Registration should be done only after all screening assessments have been performed.

Run-in phaseParticipants receiving only CRT:i)Run-in phase post CRT – week 8–10: patients will have a clinical assessment and endoscopy (sigmoidoscopy) and CT scan (run-in investigations) between week 8—10 post CRT. If there is no evidence of residual cancer found in the run-in phase investigations, subjects will have an MRI.ii)Allocation visit – week 8–10: At the allocation visit all investigations during the run-in phase will be evaluated. Patients who have achieved cCR will be allocated into the watch and wait arm. All other patients will be allocated to standard management arm.Participants receiving TNT:i)Run-in phase post TNT – week 2–3: patients will have a clinical assessment and endoscopy and CT scan (run-in investigations) between week 2–3 after the last dose of TNT. If there is no evidence of residual cancer found in the run-in phase investigations, subjects will have an MRI. If patients are required or decide to stop the doublet chemotherapy earlier than the recommended number of cycles, they will proceed to tumour response assessment 2–3 weeks after the last dose of doublet chemotherapy and allowing a minimum of 8 weeks post CRT before the response evaluation takes place.ii)Allocation visit (participants receiving TNT) – week 2–3 after the last dose of doublet chemotherapy. At the allocation visit all investigations during the run-in phase will be evaluated. Patients who have achieved cCR will be allocated into the watch and wait arm. All other patients will be allocated to standard management arm.

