#### Cost-utility analysis

In the cost-utility analysis, the effectiveness will be measured by using the QALYs (which considers both the quantity and quality of life). The health state utilities (which indicates the ‘Q’ in QALYs) will be firstly estimated based on the EQ-5D-5L questionnaire and scored using Australian-specific tariff. Alternatively, the health state utility generate from a cancer-specific quality of life instrument QLQ-C30 will also be considered to investigate the robustness of the results using a recently published Australian-specific tariff.[54] Resource use and total costs associated with the two management arms will be populated based on the data collected from the trial. Key resource use items will include rectal cancer treatment costs (such as surgery, imaging, chemotherapy, and endoscopy), and any associated healthcare costs. Both costs and benefits will be discounted by 5% in the base model, in line with government policy. Decision uncertainty will be summarised through the presentation of cost effectiveness acceptability curves.

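### The planned ICER compares complete responders with non-responders, so it mixes the effect of response with the effect of watch and wait

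*Protocol article*

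**What the plan says.** **The contrast.** Aims and objectives lists cost effectiveness as a secondary objective covering both arms. The Cost effectiveness section describes a within-trial cost-utility analysis "estimating the incremental cost effectiveness ratios (ICERs) of the watch and wait approach versus standard management plan", in which "only costs and effects that accumulate within the trial participation up to 24 months will be considered".

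**The data source.** Under Cost-utility analysis: "Resource use and total costs associated with the two management arms will be populated based on the data collected from the trial". Utilities come from EQ-5D-5L, with a second scoring from QLQ-C30 as a robustness check. "Both costs and benefits will be discounted by 5% in the base model", and decision uncertainty is shown with acceptability curves.

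**How the arms are formed.** The Design section states "This is a Longitudinal Cohort Study". Under Registration, for both the CRT-only and the TNT pathway: "Patients who have achieved cCR will be allocated into the watch and wait arm. All other patients will be allocated to standard management arm".

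**What the article says about prognosis and comparator.** Background states "Patients who achieve pathological complete response have better outcomes" and describes cCR as the surrogate for that response in patients who have not had surgery. The Discussion says the ideal study would randomise patients with a complete response between watch and wait and surgery, and explains why this was judged infeasible.

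**The concern.** Watch and wait is an option only for a patient with cCR. The alternative forgone is resection in that same patient. The standard management arm contains no such patient: it consists entirely of people who did not reach cCR and for whom watch and wait was never on offer.

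The difference in mean QALYs between the arms therefore contains the difference between responders and non-responders, and so does the difference in mean costs. The Discussion says the cost-effectiveness findings will help guide health policy. A policy reader would take an ICER labelled watch and wait versus standard management as the price of choosing one strategy over the other, and this contrast does not estimate that.

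**Working it through.** **1. The plan's own figures.** The article states no ICER, so there is none to reproduce. The arm sizes do reproduce: 47 / (1 − 0.05) = 49.5, rounded up to 50 with cCR; "Expecting 20% rate of cCR" gives 50 / 0.20 = 250 enrolled, and 250 − 50 = 200 in standard management.

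**2. Overlap on response.** Applying the allocation rule to those sizes:

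| Arm | n | With cCR |
|---|---|---|
| Watch and wait | 50 | 50/50 = 100% |
| Standard management | 200 | 0/200 = 0% |

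Arm and response are the same variable. A model with both terms cannot be identified from these data.

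**3. What the planned increment contains.** Let Q be mean 24-month QALYs, with R for responders, N for non-responders, W for watch and wait and S for standard management including resection. The planned increment is

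Q(R,W) − Q(N,S) = [Q(R,W) − Q(R,S)] + [Q(R,S) − Q(N,S)].

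The first bracket is the effect of the strategy. The second is the effect of response. The trial observes Q(R,W) and Q(N,S) but never Q(R,S), so it cannot split the sum. Costs decompose in the same way. Salvage resection after regrowth in the watch and wait arm does not supply Q(R,S), because it is part of the watch and wait pathway.

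**4. Size of the second bracket, as an illustration.** The utility gap due to response is not in the documents. I assume a range of 0.02 to 0.10, equal survival, no strategy effect, and the stated 5% discount applied to year 2:

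spurious QALY = gap × (1 + 1/1.05) = gap × 1.952.

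| Assumed gap from response alone | Spurious discounted QALY |
|---|---|
| 0.02 | 0.039 |
| 0.05 | 0.098 |
| 0.10 | 0.195 |

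It is zero only if response has no effect on utility. Better survival in responders would add to it.

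**5. Would a whole-cohort view rescue the contrast?** Compare a policy that offers watch and wait with one that does not. Non-responders get standard management under both, so, apart from any extra response assessment, they add nothing to either increment. At 20% cCR, the cost and QALY increments per enrolled patient are each 0.20 times those among responders, and the ratio is unchanged. The quantity needed is still the contrast within responders.

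**The case against.** **The article is condensed.** A fuller health-economics plan may hold adjustment methods. That would excuse missing detail, but the comparison, the data source and the within-trial limit are all stated here. A fuller plan would have to depart from this text to correct it.

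**Enrolment before CRT, and regression.** The Discussion points to early enrolment as protection against selection bias. It limits selection into the cohort but not the later split on response. The exploratory regression models under Statistical analysis are not tied to the ICER and cannot overcome a complete lack of overlap.

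**The size is assumed.** This stands. No utility gap is given, so the table shows scale and is not an estimate.

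**Stronger readings a reader might infer.** Three go beyond the documents:
- *The acceptability curve will show false certainty.* The article does not say what the curve will propagate, and with about 50 watch and wait patients it may be wide. The supportable statement is that a curve built on this contrast would not capture confounding by response.
- *TNT use differs between the arms by a calculable amount, charged to watch and wait.* The 15% and 30% in Background are pathological response rates, whereas the 20% under Sample size is clinical response. The Chemotherapy section also recommends adjuvant doublet treatment for suitable watch and wait patients who did not have TNT. The start of the 24-month cost window is not stated, so TNT costs may fall outside it. No figure can be derived.
- *The ICER is biased in favour of watch and wait.* The QALY component would be, if responders do better. The direction of the cost component cannot be derived, so the net direction is open.

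**Conclusion.** The point holds. As written, the ICER compares an arm that is all cCR with an arm that has none, and it attributes to the strategy any QALY or cost difference that comes from response. A larger sample would not help. That the confounding exists rests only on the article's allocation rule, its stated contrast and its own statement that complete responders do better, which concerns pathological response, with cCR as the surrogate. The 0.04 to 0.20 QALY range rests on the assumed utility gap of 0.02 to 0.10, equal survival and no strategy effect.

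This should be corrected before analysis. A reader might take it as a flaw in the trial as a whole, but the documents do not support that: cost effectiveness is a secondary objective, and the co-primary endpoints, which are measured in the watch and wait arm only, do not depend on it.

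**What to change.** In the Cost effectiveness and Cost-utility analysis sections:

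1. State that costs and QALYs by arm are descriptive, and that their ratio is not an ICER of the watch and wait strategy.
2. Base any ICER or acceptability curve on patients with cCR, comparing observed watch and wait with resection in the same kind of patient. The comparator can come from a decision model using the trial's surgical costs and utility changes, or from external data on complete responders who had resection.
3. If the model route is taken, add sensitivity analyses for two assumptions: that surgical costs and utility changes seen in non-responders carry over to responders, and what happens to utility between run-in and month 12, since Table 2 schedules no EQ-5D-5L or QLQ-C30 in that interval.
4. If neither source is judged adequate, report the descriptive figures and no ICER.

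Enrolment, treatment and visits do not change. The cost is a rewritten section plus either a decision model or a search for external data. The downside is a model-based ICER with wider uncertainty, or none at all.
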